#### Process Evaluation

Process evaluations are advised to monitor the implementation processes of complex interventions. In this study, the framework of the Medical Research Council guideline is followed to guide the process evaluation [31,37]. The three key functions of this framework include “implementation,” “mechanisms of impact,” and “context.” “Implementation” contains the goals and interventions that have been delivered, and how the implementation is achieved. The “mechanisms of impact” include the response to the interventions, the mediators, and all (unexpected) results and consequences. “Context” includes all other factors that may affect the implementation, interventions, and outcomes, such as barriers (eg, openness to changes, motivation, workload, and costs) and enablers [31]. In this study, we will assess these three key functions by using semistructured interviews by purposefully selecting health care professionals, team leaders, and managers 13 months after the start of the implementation. A topic guide in Dutch will be developed specifically for each hospital ward, which will consist of items covering all three key functions. In addition, 13 months after the start of the implementation, we will re-evaluate the perceived barriers and enablers to physical activity, the level of encouragement patients perceive from health care professionals and context, and their perceived self-efficacy in performing basic mobility activities independently using the survey described in step 3. We will assess the experience with our implemented interventions and various aspects of implementation fidelity (ie, adherence, exposure, and participant responsiveness) by adding both questions with a 5-point scale and open-ended questions to the patient survey (eg, “Did you receive …?” and “If so, did you find … of added value?”). We will also assess health care professionals’ perception and experience with the project and our implemented interventions by using an additional survey with open-ended questions (eg, “The following intervention does/does not add to more in-hospital physical activity …” and “Were you made aware of …?”) and by adding specific questions to our process evaluation topic guide.

### Data Analysis

All analyses will be conducted using IBM SPSS Statistics version 25 (IBM Corp). Patients’ characteristics in each cross-sectional audit will be described using descriptive statistics. Primary outcome evaluation will be performed between month 0 and month 13 across all hospital wards, and only the data of patients wearing the PAM during the entire observation period (8 AM-8 PM) will be used. The total amount of physical activity in minutes will be tested on normality with the Kolmogorov-Smirnov test and will be visually inspected using Q-Q plots. A logarithmic transformation will be considered in case of nonnormality. Analysis of covariance will be used to assess the difference in the total number of minutes of physical activity (>1.4 METs), whereby the covariates include independence in mobility and the presence of a urinary catheter. Both covariates are based on unpublished results of multivariable regression models considering various patient factors in relation to physical activity. In case nonnormality persists after logarithmic transformation, a Poisson regression model will be considered using the same covariates.

Additionally, data of behavioral mapping observations will be categorized into different activity types, from which time spent lying in bed between 8 AM and 8 PM in percentage will be derived. The difference in time patients spend lying in bed will be assessed among months 0, 6, and 13. An interrupted time series (ITS) will be used to evaluate the changes in length of stay and discharge destination among the following three predefined periods: 12 months prior to the implementation phase, 12 months implementation phase, and 6 months after finishing the implementation phase [38].

For the process evaluation, MAXQDA Analytics Plus 2018 (VERBI Software) will be used to facilitate the data analysis. All semistructured interviews will be thematically analyzed following the methods of Braun and Clarke [39]. The analytic process will be performed by two independent researchers ([name] and [name]) and supervised by [name]. Consensus meetings will be used to discuss and refine each theme. Member checking will be used to ensure the credibility of the data analysis. Triangulation of data will be performed by using the open-ended survey data during the qualitative data collection and analysis. Patient and health care professional survey results will be compared using chi-square tests and analysis of variance tests, depending on the type of data.

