**Methods:**

The Better By Moving study takes place for 12 months at the following five different wards of a university hospital: two gastrointestinal and oncology surgery wards, one internal medicine hematology ward, one internal medicine infectious diseases ward, and one cardiology ward. The step-by-step implementation model of Grol and Wensing is used, and all interventions are developed and implemented in cocreation with health care professionals and patients. Outcome evaluation is performed across the different hospital wards and for each hospital ward individually. The primary outcome is the amount of physical activity in minutes assessed with the Physical Activity Monitor AM400 accelerometer in two individual groups of patients (preimplementation [n=110], and 13 months after the start of the implementation [n=110]). The secondary outcomes are time spent in bed measured using behavioral mapping protocols, and length of stay and discharge destination assessed using organizational data. A process evaluation using semistructured interviews and surveys is adopted to evaluate the implementation, mechanisms of impact, context, and perceived barriers and enablers.

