### Setting

This study will be conducted at five different hospital wards (two gastrointestinal and oncology surgery wards, one internal medicine hematology ward, one internal medicine infectious diseases ward, and one cardiology ward) in a 1000-bed tertiary university teaching hospital Amsterdam UMC, Academic Medical Center, the Netherlands. Each hospital ward has 29 beds and a nursing-to-patient ratio of either 1:3 or 1:4, depending on the patient acuity. Allied health staffing involves 0.5 to 1 physical therapists for each hospital ward.

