### Outcome and Process Evaluation

#### Target Population

A cross-sectional audit will be conducted at baseline, 6 months, and 13 months after the start of the implementation phase. During each cross-sectional audit, a random sample of hospitalized patients will be approached to participate during one day from 8 AM to 8 PM. Eligible patients are 18 years or older, have sufficient Dutch or English speaking ability and reading skills, and are admitted for at least 24 hours. The following exclusion criteria will be used: inability to perform independent transfers prior to hospital admission, delirium, obligatory bed rest as indicated by the attending physician, expectation to be discharged before 12 AM on the day of observation, and receiving end-of-life care. Random selection of potential participants will be performed using a computer-generated list based on the room numbers of the hospital ward, and potential participants will be approached one or two days prior to the day of observation. In the case of refusal or when the patient does not meet the study criteria, the investigator will approach the patient in the next hospital room on the computer-generated list. Each participant can only be enrolled once. No a priori sample size calculations are performed. Resources allow us to spend 1 year at the iterative (cyclical) process at each hospital ward; therefore, we determined a pragmatic sample size. Considering the duration of the different steps, including three cross-sectional audits, the inclusion of 65 participants is deemed feasible at each hospital ward. Given this sample size (n=110 at baseline and n=110 at 13 months) and assuming normality of the outcome parameter, we will be able to detect an effect size of 0.38 or higher for the primary outcome (two groups *t* test of equal means; α=.05; 1−β=.80; nQuery 8, Statistical Solutions Ltd).

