Diverse factors could challenge the success of the Better By Moving study. First, several “system” factors may affect the implementation process, such as a change in the environmental context (ie, staff turnover, competing trials, and workload) and the hospital ward culture (ie, attitude to change, commitment, and motivation) [40]. For instance, the planned renovation of the participating hospital wards and the recent merger with the Vrije Universiteit Medical Center may create a lack of focus and provide additional workload. Second, because it is not known in advance which interventions will be developed and implemented, the achieved effect may differ in each hospital ward owing to differences in the interventions used. To counter this as much as possible, we will provide for both an overall and a ward-specific analysis. Third, changing the health care professionals’ and patients’ behaviors toward in-hospital physical activity through the development and implementation of multiple interventions in cocreation takes time. While we have 12 months for each hospital ward to cocreate interventions, important changes in hospital culture, environmental context, and outcomes may arise after the last cross-sectional audit. Lastly, a pre-post mixed-methods design is used to investigate if interventions developed and implemented in cocreation improve physical activity among patients. To evaluate the effect of an intervention, a randomized controlled trial is considered the gold standard. With respect to cocreational bottom-up intervention development and implementation, in which the process, to a large extent, determines the outcome, it is considered not feasible to use a control group. Instead, we aim to evaluate the impact of our interventions on physical activity as representative as possible by approaching a random sample of at least 110 hospital patients using a computer-generated list based on hospital room numbers before and after the implementation of interventions.

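### The pooled primary model omits ward although patients are sampled ward by ward, and the promised ward-level results would rest on about 22 versus 22 patients

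*Protocol article*

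**What the plan says.** The primary comparison is pooled: "Primary outcome evaluation will be performed between month 0 and month 13 across all hospital wards" (Data Analysis). The model is an analysis of covariance with two named covariates, mobility independence and whether a urinary catheter is present. The section gives one reason for both, an unpublished regression on patient factors. The Poisson model held in reserve for persistent non-normality uses the same covariates. Only patients who wore the monitor for the whole 8 AM to 8 PM window are analysed.

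The design is organised by ward. Setting states: "This study will be conducted at five different hospital wards". These are two gastrointestinal and oncology surgery wards and one each of hematology, infectious diseases and cardiology. Under Target Population, patients are drawn at random from each ward's room list, and "including three cross-sectional audits, the inclusion of 65 participants is deemed feasible at each hospital ward".

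The detectable effect is given once, for the pooled comparison: "Given this sample size (n=110 at baseline and n=110 at 13 months"), "we will be able to detect an effect size of 0.38 or higher for the primary outcome" (Target Population).

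Ward-level results are also promised. The abstract says "Outcome evaluation is performed across the different hospital wards and for each hospital ward individually". The Discussion expects that "the achieved effect may differ in each hospital ward owing to differences in the interventions used" and offers a ward-specific analysis alongside the overall one in response.

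**The concern.** Ward is a design stratum: recruitment, audit and intervention are all run ward by ward. An analysis that ignores a stratum has two possible costs.

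- **Balanced ward numbers.** The pre-post difference is not biased by ward, but differences in activity level between specialties stay in the residual and precision is lost.
- **Unbalanced ward numbers.** Part of the difference between month 0 and month 13 is a difference in which wards the patients came from. The study is uncontrolled, so no comparison group would reveal this.

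The separate ward-specific analysis does not repair the pooled model. It also has far fewer patients than the comparison for which 0.38 was calculated. A reader could take a clear result in one ward and an unclear one in another as evidence that one ward's interventions worked and the other's did not.

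**Working it through.** **Inputs from the protocol article.** 110 versus 110 independent patients and effect size 0.38; "α=.05; 1−β=.80; nQuery 8"; five wards; 65 patients per ward over three audits. No SD, ward mean or intraclass correlation is given, so the variance shares below are assumptions.

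**1. The stated figure.** SE of the standardised difference = √(2/110) = 0.135. Normal approximation: (1.960 + 0.842) × 0.135 = 0.378. With the noncentral t and a two-sided 5% test, the detectable effect is 0.379 and power at 0.38 is 80.1%. The stated 0.38 is reproduced. A one-sided test would give 0.336, so the figure is two-sided.

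**2. Patients per ward per audit.** 110/5 = 22 and 65/3 = 21.7. The totals also agree closely: 5 × 65 = 325 against 3 × 110 = 330. Twenty-two is a derived average, not a stated quota.

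**3. Balanced wards, ward omitted.** Let ρ be the share of variance that ward explains beyond the two covariates (assumed). With ward in the model the residual SD shrinks by √(1−ρ), so the detectable effect is 0.379 × √(1−ρ). With ward omitted, and no drift of wards between audits, the nominal 5% test has actual size 2 × [1 − Φ(1.96/√(1−ρ))].

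| ρ (assumed) | Detectable effect with ward | Power at 0.38 with ward | CI narrower by | Size of the test without ward |
|---|---|---|---|---|
| 5% | 0.370 | 82% | 2.5% | 4.4% |
| 10% | 0.360 | 84% | 5% | 3.9% |
| 20% | 0.339 | 88% | 11% | 2.8% |

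**4. Unbalanced wards.** If k patients out of 110 come from one ward instead of another at one audit, the pooled difference shifts by (k/110) × the gap between those wards' means. As an illustration of scale only, k = 4 and an assumed gap of 1 SD give 4/110 = 0.036 SD, or 0.036/0.135 = 0.27 SE. The documents give neither the likely k nor the gap.

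**5. Ward-level comparison, 22 versus 22.** SE = √(2/22) = 0.302 SD. Detectable effect at 80% power (noncentral t): 0.86 SD, which is 0.86/0.38 = 2.3 times the pooled figure. Power at 0.38: 23%. Half-width of the 95% CI: 2.018 × 0.302 = 0.61 SD. These are in within-ward SDs. If ρ were 20%, 0.86 would be 0.86 × √0.8 = 0.77 in the pooled SD, still about twice 0.38.

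**6. Wards that drift independently between audits.** With about 22 patients per ward per audit and an assumed ward-by-period correlation r, the variance of the pooled difference is multiplied by 1 + 21r. For r = 0.01/0.02/0.05 this is 1.21/1.42/2.05. The nominal 5% test then has size 2 × [1 − Φ(1.96/√(1+21r))] = 7.5%/10%/17%. A ward main effect does not change this.

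**The case against.** The best case for leaving the plan alone is that the gain is small. At a ward share of 5 to 10% the detectable effect moves only from 0.38 to 0.37 or 0.36. The share that counts is what remains after mobility and catheter, and both may differ by specialty and absorb part of it. With balanced wards nothing is biased. This stands, and it limits the size of the point, but it is no reason to omit a stratum that costs four degrees of freedom. One could add that the covariate list is worded openly. However, the section justifies both covariates as a pair and reuses them in the fallback, so a model without ward is the plain reading.

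Several stronger readings are tempting, and the documents do not support them:

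- *Refusals distort the ward mix.* A refusal is replaced by the patient in the next room on the ward's own list. That changes who is sampled within the ward, not how many the ward contributes. What remains open is the absence of a stated quota per ward per audit and the restriction to complete wearers, for which no loss rate is given.
- *Ward numbers are fixed by design.* The 65 per ward is described as feasible over three audits, not as a quota.
- *A bias in minutes can be stated.* It cannot, because no ward means or SD are given.
- *The pooled test is simply conservative.* That holds only if wards do not drift independently between audits. With drift the error goes the other way (step 6).
- *The ward analyses carry a 23% familywise error.* 1 − 0.95⁵ = 0.226 applies only if five unadjusted tests at .05 are run. The protocol promises ward-level evaluation and specifies no such tests.

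**Conclusion.** The point holds as an inexpensive improvement, not as a flaw that invalidates the primary analysis. The pooled model and its fallback omit the factor by which patients are sampled. With similar ward numbers at both audits the cost is precision: a detectable effect of 0.38 where about 0.37/0.36/0.34 could be had, if ward explains an assumed 5/10/20% of the variance remaining after the covariates. With unequal ward numbers, ward differences also enter the period effect, by an amount the documents do not allow one to estimate.

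The ward-level results can show only large effects, about 0.86 SD at an average of 22 versus 22, with about 23% power at the plan's own 0.38. They can describe the wards, but they are too imprecise to establish that a moderate effect is present in one and absent in another.

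The precision figures refer to the linear model and rest on assumed variance shares and balanced wards. The ward-level figures rest on the derived average of 22, which incomplete wear would lower.

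**What to change.** 1. Add ward as a five-level fixed factor to the primary analysis of covariance and to the Poisson fallback. This costs four degrees of freedom and one sentence, and uses data already held.
2. Estimate the promised ward-specific effects from one ward-by-period model rather than five separate analyses. Report them with confidence intervals, label them exploratory, and base any statement that wards differ on the interaction. This costs four further degrees of freedom, in that secondary model only.
3. Report the number analysed per ward at each audit, so that readers can see whether the ward mix changed.
4. State as a limitation that a ward main effect does not account for wards changing independently between audits for reasons other than the interventions, and that an uncontrolled comparison of five wards cannot separate such drift from effect.

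None of these changes needs additional patients or measurements.

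### Normality is checked on the activity minutes instead of the ANCOVA residuals, so prognostic, skewed covariates can prompt an unnecessary transformation or fallback model

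*Protocol article*

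**What the plan says.** All of this is in the Data Analysis section, in the order of the text:

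- The variable checked is the outcome itself: "The total amount of physical activity in minutes will be tested on normality with the Kolmogorov-Smirnov test and will be visually inspected using Q-Q plots".
- First consequence: "A logarithmic transformation will be considered in case of nonnormality".
- The primary model is an analysis of covariance of minutes above 1.4 METs between month 0 and month 13, "whereby the covariates include independence in mobility and the presence of a urinary catheter".
- Origin of the covariates: "Both covariates are based on unpublished results of multivariable regression models considering various patient factors in relation to physical activity".
- Second consequence: "In case nonnormality persists after logarithmic transformation, a Poisson regression model will be considered using the same covariates".

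The sample-size paragraph under Target Population uses the same framing: "Given this sample size (n=110 at baseline and n=110 at 13 months) and assuming normality of the outcome parameter". A detectable standardised difference of 0.38 is claimed on that basis. Residuals are mentioned nowhere in the article.

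**The concern.** The check bears on which model, and which scale, gives the primary result, but it examines the wrong quantity. ANCOVA needs errors that are normal given period, mobility and catheter. The distribution of the minutes mixes those errors with the spread of the covariates.

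The design makes a discrepancy plausible. The covariates were chosen because they relate to activity. One is binary. The other is a short-form mobility score (Secondary Outcomes). Target Population excludes patients who could not transfer independently before admission and those on obligatory bed rest, so scores may crowd near the top. The better these covariates predict activity, the more likely the check is to flag a non-normality that the model already accounts for. The estimate would then move from minutes to log minutes, or to a rate ratio, for a reason unrelated to the validity of the ANCOVA.

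**Working it through.** **1. The plan's own figure.** Inputs from Target Population: 110 per audit, α=.05 (taken as two-sided; not stated), power .80.

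- n per group = 2(1.960+0.842)²/0.38² = 2×7.85/0.1444 = 108.7, so 109.
- Detectable effect at 110 per group = 2.802×√(2/110) = 0.378. The exact noncentral t gives 0.379, with power 0.801 at 0.38.

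The stated 0.38 reproduces and is not affected by this point.

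**2. Why the outcome check misleads.** Write minutes = covariate part S + normal error, with no period effect, and let R² be the share of variance due to S. The error has no skewness, so

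skewness(minutes) = (R²)^1.5 × skewness(S), while the errors have skewness 0.

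With a mobility score piled up at its ceiling and 25% catheter use (both assumed), simulated mean skewness of the minutes was −0.09, −0.15, −0.24, −0.33 and −0.44 at R² = 0.2, 0.3, 0.4, 0.5 and 0.6. The last value gives skewness(S) = −0.44/0.6^1.5 = −0.44/0.465 = −0.95. The formula then predicts 0.4^1.5 × (−0.95) = 0.253 × (−0.95) = −0.24 at R² = 0.4, as simulated. Taking logs makes a left skew worse.

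**3. How often the check raises a false alarm.** Assumptions, none of them in the article: 110 vs 110 analysed together; no period effect; errors exactly normal on the log scale; log SD 0.8; 20% with a catheter; mobility bounded 6-24 with ceiling crowding; Kolmogorov-Smirnov test corrected for estimated parameters (Lilliefors); automatic switch at p<0.05. The ranges cover repeated runs that differ in replicates and covariate weighting. Entries are the share of trials in which non-normality is declared on both the raw and the log scale, so that the Poisson step is reached.

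| R² | 0.2 | 0.3 | 0.4 | 0.5 |
|---|---|---|---|---|
| Outcome checked, strongly skewed score | 5-8% | 10% | 17-20% | 32-38% |
| Outcome checked, less skewed score | 4-6% | 7% | 10-11% | 17-18% |
| Residuals checked | 4-5% | 4-5% | 4-5% | 4-5% |

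With errors normal on the raw-minutes scale and the strongly skewed score, the outcome check reached the fallback in 6%, 9%, 18% and 34%, against 3-4% on residuals. Under the ceiling and 25% catheter assumptions of step 2, the first check alone rejected in 4-5% at R² ≤ 0.2, 7% at 0.3, 12-13% at 0.4, 22% at 0.5 and 41-42% at 0.6, against 3-6% on residuals. With crowding at the floor of the score instead, it rejected in only 4% at 0.4 and 13% at 0.6.

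**4. What happens to type I error.** In the log-scale scenario with the skewed score, an automatic cascade ending in an unscaled Poisson model has type I error of 9-10%, 11-13%, 16-18% and 26-28% at R² = 0.2 to 0.5. Two single changes separate the causes:

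- Keep the outcome check, scale the Poisson variance for dispersion: about 4-7%.
- Check residuals, keep the unscaled Poisson: about 7-10%.

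The mechanism is the usual one. With dispersion φ, the unscaled test rejects with probability 2Φ(−1.96/√φ), which is 17% at φ=2 and 38% at φ=5. With an assumed mean of 60 and SD of 20 minutes, simulated φ was about 3 to 5.5 and unscaled Poisson rejected in 24-40%. Scaled Poisson gave 4-6%.

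**5. Sensitivity.**

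- With the uncorrected Kolmogorov-Smirnov test and normal errors, the outcome check fails on both scales in at most about 1-2% of trials.
- With gamma-distributed minutes given the covariates, the fallback is reached in 52-86% of trials with the outcome check and 59-96% with residuals.
- With exponential-type errors, ANCOVA at 110 vs 110 still had 5.5% type I error.

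**The case against.** Several counter-arguments have force.

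- *No automatic gate.* Both fallbacks are only to be considered, and Q-Q plots are read beside the test. This stands, so the rates above are upper figures. It does not remove the point, because the Q-Q plots are also of the minutes and mislead in the same direction.
- *The second check names no variable.* The Poisson sentence does not say what is examined after the log transformation; residuals of the log model are not excluded. This stands. Only the first check is explicitly on the outcome, so the route to Poisson is conditional on that check being repeated on the log minutes.
- *The test version is not stated.* With the uncorrected test the false alarm almost disappears. This stands as a limit on the size.
- *Residual checks do not always reduce use of the fallback.* With gamma errors they reach it somewhat more often. This also stands. There the errors really are non-normal, and the remedy is a sound variance in the fallback rather than the choice of variable.
- *An article condenses.* A fuller analysis plan may already check residuals. If so, only the wording needs aligning. But the article does name a variable, so this is a stated choice and not a detail left out.

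A reader might also infer that the check inflates the primary type I error to as much as 26-28%. The working does not support that: scaling the Poisson variance removes nearly all of it with the outcome check left in place, and moving the check to residuals alone does not. The article does not say whether the Poisson variance would be scaled, so the inflation cannot be attributed to the normality check.

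**Conclusion.** The stated check is on the wrong quantity for an ANCOVA. It can prompt an unnecessary log transformation or, if repeated on the log outcome, consideration of Poisson regression while the ANCOVA is valid. The conceptual point is certain; its size is conditional.

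With normal errors, a corrected Kolmogorov-Smirnov test and an automatic switch, the excess is small at a covariate R² of about 0.2 or less. With a strongly skewed mobility score it reaches roughly 20% of trials at 0.4 and 30-40% at 0.5, against about 5% for residuals. It is about half that with a less skewed score. R², catheter prevalence, score distribution and SD of the minutes are all assumed. The simulations also analysed the two audits together; the article does not say whether they would be examined together or separately, and neither choice removes the covariates.

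The harm that can be credited to this point is a needless change of scale and estimand, not a quantified loss of type I error control. Minor to moderate priority.

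**What to change.** In Data Analysis, replace the normality sentence so that it says:

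- Normality is assessed on the residuals of the ANCOVA with period, independence in mobility and urinary catheter. If a log transformation is used, it is assessed again on the residuals of the log-scale ANCOVA before any fallback.
- The assessment is mainly by Q-Q plot. Any Kolmogorov-Smirnov test is supportive and uses the version corrected for estimated parameters.
- Any Poisson fallback uses a dispersion-scaled or robust variance. This second change is needed because checking residuals alone does not remove the error inflation described above.

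The cost is two or three sentences and saving the model residuals at analysis. No data, patients or power are lost, and the 0.38 detectable effect is unchanged.

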## Methods

### Study Design

An uncontrolled pre-post embedded mixed-methods study is designed to evaluate whether we can improve physical activity in hospitalized patients by using interventions that we develop and implement in cocreation. The development and implementation describe the iterative (cyclical) process of planning, conducting, reflecting, and refining, which is being used in close collaboration with local stakeholders, such as patients, health care professionals, and managers [19]. The study has been approved by the Medical Research Ethics Committee of the Amsterdam University Medical Centers (Amsterdam UMC), Academic Medical Center (W17_479 #18.003 and W19_213 #19.258). Written informed consent will be obtained from all participants in both the outcome and process evaluations.

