#### Secondary Outcomes

Secondary outcomes include the time patients spend in bed, length of stay, and discharge destination. Data on the time patients spend in bed will be measured during each of the cross-sectional audits using the behavioral mapping method [26-28]. In detail, structured observations will be undertaken by trained physical therapy graduate students for a 1-minute period every 10 minutes between 8 AM and 8 PM, using a predetermined set of mutually exclusive types of activities (lying in bed, sitting on the edge of a bed or sitting in a chair, making a transfer from bed to chair, or standing, walking, and using the ergometer). For each minute of observation, the activity with the highest intensity is recorded. Patients are not followed off the ward and not intruded on if behind closed curtains. In addition, the following patient characteristics will be collected during each of the cross-sectional audits: sex, age, comorbidities, number of functional restraints (eg, intravenous lines and drains), functional ability with the Katz-ADL 2 weeks before admission [35], and independence in mobility using the Activity Measure for Post-Acute Care “six clicks” Basic Mobility Short Form [36]. Data will be directly recorded in the online Castor Electronic Data Capture database (Ciwit BV).

Data on length of stay and discharge destination will be obtained from the hospital administrative data for all patients admitted to the surgery, internal medicine, and cardiology hospital wards. Discharge destination will be categorized as follows: going home or going to a temporary institution (ie, nursing home, geriatric rehabilitation center, or medical rehabilitation center). Data on patients who are discharged to a permanent nursing home or other hospitals, those who receive end-of-life care (at home or at a facility), or those who die during hospitalization will be omitted because other influences (such as illness, prognosis, and cognitive function) determine the outcome.

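### The primary month-13 versus month-0 model adjusts only for current mobility and urinary catheter, so case-mix differences in age, sex, comorbidity and pre-admission function, all recorded, may be partly read as a programme effect

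*Protocol article*

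**What the plan says.** Study Design states the design plainly: "An uncontrolled pre-post embedded mixed-methods study is designed to evaluate whether we can improve physical activity in hospitalized patients". The Abstract (Methods) gives the primary contrast as two separate groups, 110 before implementation and 110 at 13 months. Under Target Population, "Each participant can only be enrolled once", so no patient is measured twice. Sampling within an audit is random: "Random selection of potential participants will be performed using a computer-generated list based on the room numbers of the hospital ward".

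Under Secondary Outcomes, each audit records "sex, age, comorbidities, number of functional restraints (eg, intravenous lines and drains), functional ability with the Katz-ADL 2 weeks before admission", together with current independence in mobility on the AM-PAC short form.

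Under Data Analysis, patients' "characteristics in each cross-sectional audit will be described using descriptive statistics". The primary model is an analysis of covariance of active minutes, month 13 against month 0, "whereby the covariates include independence in mobility and the presence of a urinary catheter". The reason given is that both came from earlier, unpublished multivariable models of activity; the factors those models examined are not listed. If normality fails even after log transformation, a Poisson model with the same covariates is considered. The verb 'include' does not formally close the list, but the references to both covariates and to the same covariates read as a set of two.

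**The concern.** With no concurrent control and no patient acting as their own control, the comparability of month-0 and month-13 patients rests on the model. Random sampling makes each audit representative of its own time. It does not make the two times exchangeable. Refusers and ineligible patients are replaced, and only patients with complete 8 AM to 8 PM wear are analysed, so selection may also differ between audits.

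Age, sex, comorbidity and pre-admission function are settled before the ward programme can act, which makes them the safest case-mix adjusters available. Neither planned covariate describes the patient before admission. Choosing covariates by their association with activity also addresses only half of confounding: it cannot show whether a factor differs between the audits.

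At stake is the primary conclusion. If month-13 patients are fitter in ways that mobility and catheter do not capture, activity rises without any programme effect. If they are frailer, a real effect is masked.

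**Working it through.** **1. Reproduce the plan's own figure.** Inputs from Target Population: 110 per group, α = .05, power .80, two-group t test.

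- Normal approximation: detectable effect = (1.960 + 0.842) × √(2/110) = 0.378.
- Two-sided noncentral t: 0.379, with power 80.1% at 0.38.

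The stated 0.38 reproduces and is not in dispute.

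**2. What an omitted factor does.** Let b be the slope of activity on the factor given mobility and catheter (outcome SD per factor SD). Let s be the factor's between-audit shift that remains given those covariates (factor SD). With no programme effect, the apparent effect is

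bias = b × s.

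It is zero if either term is zero. The documents give neither, so the values below are assumptions.

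**3. Effect on the test.** Noncentrality = bias × √(110/2) = bias × 7.416, referred to the two-sided 5% t test.

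| b | s | bias (SD) | noncentrality | rejection when there is no effect |
|---|---|---|---|---|
| 0 | any | 0 | 0 | 5.0% |
| 0.1 | 0.3 | 0.03 | 0.222 | 5.6% |
| 0.2 | 0.3 | 0.06 | 0.445 | 7.3% |
| 0.3 | 0.3 | 0.09 | 0.667 | 10.2% |

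Against the detectable effect, 0.03/0.38 = 8% and 0.09/0.38 = 24%.

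**4. How much the planned covariates absorb.** Suppose the omitted factor shifts by a total S, and mobility correlates ρ with it and moves only because of it. Adjusting for mobility then leaves a shift of S × (1 − ρ²), so the residual bias is b × S × (1 − ρ²). A simulation of the planned analysis of covariance checks this (110 per group, 4,000 runs per row; mobility slope 0.4, catheter slope 0.2 and catheter prevalence 30%, all assumed). Biases are absolute values.

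| b | S | ρ | b·S·(1 − ρ²) | simulated bias | rejection, planned model | rejection, factor added |
|---|---|---|---|---|---|---|
| 0 | 0.3 | −0.3 | 0 | 0.003 | 5.9% | 4.2% |
| 0 | 0.3 | −0.6 | 0 | 0.000 | 5.2% | 5.5% |
| 0.2 | 0.3 | −0.3 | 0.055 | 0.056 | 7.8% | 5.2% |
| 0.2 | 0.3 | −0.6 | 0.038 | 0.042 | 6.0% | 4.6% |
| 0.3 | 0.3 | −0.3 | 0.082 | 0.080 | 9.5% | 4.7% |
| 0.3 | 0.3 | −0.6 | 0.058 | 0.060 | 7.2% | 4.4% |

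The simulation error near 5% is √(0.05 × 0.95/4000) = 0.34 percentage points. Mobility reduces the bias without removing it. Adding the factor brings the bias to about zero and rejection to about 5%.

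**The case against.** The best defence is that case mix is already partly adjusted. Mobility and catheter use both carry case-mix information, and whatever age or prior function does through mobility is removed with it. If the earlier models tested these four factors and found nothing beyond mobility and catheter, omitting them does little harm. Wards, eligibility rules and room-based selection are also the same at each audit, and patients who could not transfer independently before admission are excluded, which narrows the range of Katz-ADL. This stands as a limit on the size of the problem. It does not dispose of it, because the earlier models are unpublished, their candidate factors are not named, and identical selection rules do not hold the admitted population constant.

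Several stronger readings are tempting but unsupported:

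- That any case-mix change will be read as a programme effect. Only the part not captured by mobility and catheter can be, and its direction is unknown.
- That the renovation and merger named in the Discussion will change who is admitted. The article links them only to focus and workload.
- That time in bed is left wholly unadjusted. The article says only "The difference in time patients spend lying in bed will be assessed among months 0, 6, and 13" and names no model, so an unadjusted analysis is not fixed.
- That chance imbalance between the samples adds bias. The standard error and the 5% level already cover it.
- That adjustment would improve the 0.38 by a calculable amount. That figure belongs to an unadjusted t test, and the variance explained beyond mobility and catheter is unknown.

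One could also hold that a sensitivity analysis would be enough. That is defensible as a minimum, but the larger model costs almost nothing.

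**Conclusion.** The concern holds as possible residual confounding in the primary comparison. The article fixes the covariate set and its rationale, so this is a choice made and not a detail left to another document. The size cannot be determined from the article. It is nil if the four factors carry no association with activity given mobility and catheter, or do not shift between audits given those two. Under assumed residual biases of 0.03 to 0.09 SD, about 8% to 24% of the detectable effect, the false-positive rate rises from 5% to roughly 6% to 10%. An opposite shift would hide a real effect to the same extent. This is a change that should be made; it does not invalidate the study.

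**What to change.** In Data Analysis, prespecify age, sex, comorbidity (count or index) and Katz-ADL two weeks before admission as covariates in the month-13 versus month-0 model, in addition to mobility and catheter. Carry the same set into the Poisson fallback. Report the unadjusted difference and the two-covariate result beside it, so that readers can see how far the estimate moves.

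The cost is one or two sentences and no new data collection. With one term each for mobility and catheter and up to 220 analysed patients, the residual degrees of freedom go from 220 − 4 = 216 to 220 − 8 = 212. A few missing covariate values will need a stated rule.
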